## **LIST OF ABBREVIATIONS**

**FMD:** Functional Motor Disorders

**HC:** Healthy controls

**CNS:** Central Nervous System

**Unit 1:** Veneto, AOUI Verona/DAI Neuroscienze/Università di Verona

**Unit 2:** AOU San Giovanni e Ruggi da Aragona; Università di Salerno/AOU San Giovanni e Ruggi D'Aragona

**Unit 3:** IRCCS Ospedale San Raffaele; Division of neuroscience

**EEG:** electroencephalogram

**MRI:** Magnetic Resonance Image

**3T:** 3 Tesla

**ET:** essential Tremor

**QoL:** Quality of Life

**EMG:** Electromyography

**HPT:** objective/subjective Heart Rate HR, ratio

**fMRI:** function magnetic resonance imaging

**WP:** work packages

**IRFMD:** Italian Registry of Functional Motor Disorders

**SFMDRS:** Simplified Functional Movement Disorders Rating Scale

**MFI:** Multidimensional Fatigue Inventory Scale

**BAI:** Beck Anxiety Inventory

**BDI-II:** Beck Depression Inventory

**SF-12:** Short-Form Health Survey

**XAI:** explainable artificial intelligence

## ABSTRACT

Functional motor disorders (FMD) are part of the wide spectrum of functional neurological disorders characterized by abnormal movements (functional limb weakness, tremor, dystonia) that are significantly altered by distractive maneuvers and are incongruent with movement disorders seen in specific neurological diseases. FMD have a high prevalence, are still misunderstood, diagnosed with a long delay, and not properly treated, leading to high degrees of disability and poor quality of life with increasing social and economic costs. The old concept of psychological factors as the primary cause (conversion disorder) has been abandoned due to the lack of evidence about their causal role. According to a predictive coding account, the emerging idea is that symptoms and disability in FMD may depend on dysfunctions of a specific neural system integrating interoception, exteroception, and motor control. The idea that underpins our proposal is that FMD symptoms are perceptions of the state of the body. Besides the main pathophysiological features (abnormal attentional focus, beliefs/expectations, and sense of agency), the lived experience of symptoms and their resulting disability may depend on a specific neural system integrating motor, exteroceptive and interoceptive domains. Therefore, dysfunction within this system can cause and sustain motor and non-motor symptoms in FMD. Three-stage research will be conducted. A large cohort of patients with a definite diagnosis of FMD (n=150) and healthy controls (n=150) will be investigated by behavioral, neurophysiological, and MRI tests to collect biomarkers in the motor, exteroceptive and interoceptive domains. Computational modeling of the behavioral, neurophysiological, and MRI biomarkers will be developed through eXplainable Artificial Intelligence (XAI) methods through a data mining approach (machine learning) to implement a diagnostic algorithm biomarker (objective 1). A cohort of patients with "organic" motor disorders (n=75) will undergo the same behavioral, neurophysiological, and MRI tests belonging to the resulting biomarker-based diagnostic algorithm for validation (objective 2). Finally, the modulation of the resulting biomarker-based diagnostic algorithm after rehabilitation and the correlations of motor and non-motor symptoms (NMSs) with clinical improvement will be investigated in a sub-group of patients with FMD to explore the prognostic value (objective 3). Our proposal consists of 6 work packages (WP), all integrated to deliver our stated objectives over the project's lifetime to achieve these objectives. Communication and dissemination activities will include the project's visual identity, public website, social media, videos, and press releases. Our proposal will inform the research and clinical community on disease-specific biomarkers to serve for the diagnosis and prognosis of patients with FMD. The proposed approach has significant potential to disentangle some of the poorly understood features of these disorders, potentially providing a platform for more fundamental insights into brain functioning and development of precision medicine approaches in their management. The proposed approach also can provide the clinicians with a set of validated examinations to make a correct early diagnosis. This will improve the management of FMD with a positive impact on the patient's disability and socio-economic costs of the illness.

## **1. BACKGROUND/STATE OF THE ART**

FMD is characterized by abnormal movements significantly altered by distractive maneuvers and incongruent with movement disorders seen in typical neurological diseases. They represent more than 50% of functional neurological disorders, which have an incidence of 4-12/100.000 per year and a prevalence of 50/100.000 in patients admitted to Neurological clinics. FMD include highly disabling disorders with poverty (weakness and slowness) or movement excess (tremor, dystonia). They can have isolated or combined motor symptoms and other functional disorders and complain of non-motor symptoms (fatigue, pain), contributing to disability and poor quality of life. The pathophysiology of FMD remains still unknown. According to a predictive coding account, the emerging idea is that symptoms are perceptions of the state of the body. Therefore, they rely on neural processes that actively sample body information and process it into conscious percepts. The brain uses such percepts to control motor and behavioral responses, producing sensory feedback. Thus, symptoms and disability in FMD may depend on dysfunctions of a specific neural system integrating interoception, exteroception, and motor control. Scientific and clinical developments have provided a strong rationale and scientific foundation for identifying specific biomarkers for FMD diagnosis and prognosis. It will improve the early identification of FMD patients and maximize the efficacy of multidisciplinary patient management.

## **2. EXPERIMENTAL DESIGN**

### **Experimental study without drug or medical device**

#### **Experimental design aim 1**

This is a cross-sectional study that will involve 150 patients with a clinically definite diagnosis of FMD based on Gupta and Lang diagnostic criteria (1) and 150 matched HC consecutively recruited by Unit 1 (75 patients and 75 HC) and Unit 2 (75 patients and 75 HC) (WP1). Healthy controls, matched for age and sex, will be recruited through public advertisements. We will develop behavioral, neurophysiological, and MRI biomarkers for each patient and HC in the motor, exteroceptive, interoceptive and cerebral domains (see methods, data collection section). Unit 1 and 2 will perform the same behavioral, neurophysiological, and MRI tests on FMD and HC. 3T MRI data will be processed by Unit 3 to estimate brain structural and functional MRI features of sensorimotor and non-motor networks (WP2). The diagnostic biomarker algorithm through eXplainable Artificial Intelligence (XAI) methods will be developed by Unit 2 (WP3).

#### **Experimental design aim 2**

Cross-sectional design on a total of 150 additional patients with "organic" motor disorders (50 patients with weakness due to peripheral neuromuscular disorders; 50 with essential tremor [ET] according to the 2018 consensus criteria (2); 50 with idiopathic adult-onset dystonia) recruited by Unit 1 (75 patients) and 2 (75 patients) (WP4). The same diagnostic biomarker algorithm identified in experiment 1 will be tested in patients with organic motor disorders (WP4) to identify disease-specific hallmarks of FMD. Structural and functional MRI data will be processed by Unit 3. The diagnostic biomarker algorithm through XAI methods will be tested by Unit 2.

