### **3. PROJECT AIMS**

#### **Specific aim 1**

To develop a biomarker-based diagnostic algorithm for FMD by modeling behavioral, neurophysiological, and MRI biomarkers to investigate the motor, exteroceptive and interoceptive domains. Deep learning will be used, and visualization and interpretability methods will be exploited to identify the most sensitive measures. The results obtained will determine which biomarkers are the hallmarks for FMD diagnosis identifying the key differences between FMD and healthy controls.

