#### **Specific aim 2**

To test the validity of the resulting biomarker-based diagnostic algorithm against patients with "organic" motor disorders to evaluate its specificity for FMD. The results obtained will determine which biomarkers are specific for FMD diagnosis identifying the key differences between FMD and patients with "organic" motor disorders.

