The implementation of machine learning algorithms will be done using the KNIME analytics platform (v. 4.2.1), widely used in biomedical studies. **The software is for research purposes only and not for diagnostic purposes. Data analysis will be anonymized for privacy protection, removing personally identifiable information from data sets (i.e., patients' number will be changed into a range of values with logical boundaries).** In this study, binary supervised classification will be applied with learning derived from decision tree-based (tree-based) and instance-based (instance-based) algorithms. Machine learning input features will include clinical and neurophysiological variables and data extracted from neuroradiological imaging. Feature importance will also be calculated using the Random Forest algorithm to identify the most relevant input features for classification.

### Experimental design 2

The same diagnostic biomarker algorithm identified in experiment 1 will be tested in patients with organic motor disorders (WP4) to identify disease-specific hallmarks of FMD. Structural and functional MRI data will be processed by Unit 3. The diagnostic biomarker algorithm through XAI methods will be tested by Unit 2.

### Experimental design 3

A physician expert in movement disorders will assess patients at each time point through validated clinical scales to assess motor and non-motor symptoms, depression, anxiety, alexithymia, and QoL as reported in the Methodologies section. A task-based fMRI paradigm to evaluate functional brain reorganization of sensorimotor and non-motor networks induced by rehabilitation and correlations with clinical improvement will be

implemented and performed before rehabilitation (T0) and at 3-month follow-up (T1) (5,6). fMRI data will be analyzed by Unit 3. The diagnostic biomarker algorithm through XAI methods will be tested by Unit 2 before and after rehabilitation.

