## 12. STATISTICAL ANALYSIS

eXplainable AI (XAI) analysis. First, ad-hoc models will be identified based on the available data, accounting for type (multi- modal), numerosity, completeness (missing data). Then, the models will be trained and validated following k-fold cross- validation and finally tested on a new (unseen) set of data to assess their generalization properties. Classical linear methods that are the most widespread in the clinical field will be used for benchmarking. Finally, we will apply XAI methods for assessing feature relevance, and consensus will be assessed under the assumption that this will provide information about the robustness of the outcomes (27-29). This will also be investigated through association studies with parameters holding clinical relevance.

Firstly, we will employ XAI analysis using the dataset from the first recruited 150 subjects (75 FMD and 75 HC). Secondly, external validation will be performed on an independent dataset of features collected on an additional sample of 150 subjects (75 FMD and 75 HC). Finally, the biomarkers identified in the diagnostic biomarker algorithm (experiment 1) will be tested against patients with organic neurological disorders recruited by Unit 1 and 2.

For the rehabilitation sub-study, descriptive statistics will include frequency tables for categorical variables and mean and standard deviation for continuous variables. The normality of data distribution will be checked with the Shapiro-Wilk test. Parametric (paired t-test) or non-parametric tests (Wilcoxon test) will be applied accordingly to compare the means for the two-time points (T0, T1). fMRI data will be analyzed using the SPM12 software. One-sample t tests will be used to evaluate significant mean brain activations during the task. Changes over time will be evaluated using a paired t test. All the longitudinal data deriving from the rehabilitation sub-study will be handled with a complex approach named Gaussian Process Panel Modeling (GPPM). GPPM provides great flexibility because of the large number of models it can represent. It allows classical statistical inference as well as machine learning inspired predictive modeling, with the advantage of obtaining person-specific predictions of treatment response (30).

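### Aim 2 as described estimates the specificity of an FMD-versus-healthy algorithm in organic patients, but does not show which biomarkers separate FMD from organic disease, which it also promises

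*Protocol*

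**What the plan says.** **How the algorithm is built.** Section 6 fixes a two-class model: "In this study, binary supervised classification will be applied with learning derived from decision tree-based (tree-based) and instance-based (instance-based) algorithms". Section 12 gives the development set: "Firstly, we will employ XAI analysis using the dataset from the first recruited 150 subjects (75 FMD and 75 HC"). It then adds that "external validation will be performed on an independent dataset of features collected on an additional sample of 150 subjects (75 FMD and 75 HC"). Neither set contains organic patients. Specific aim 1 says what the selected markers mean: the results will determine "which biomarkers are the hallmarks for FMD diagnosis identifying the key differences between FMD and healthy controls".

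**What aim 2 does.** Section 2 (aim 2) and section 6 (experimental design 2) carry the algorithm over unchanged: "The same diagnostic biomarker algorithm identified in experiment 1 will be tested in patients with organic motor disorders (WP4) to identify disease-specific hallmarks of FMD". Section 12 says that "the biomarkers identified in the diagnostic biomarker algorithm (experiment 1) will be tested against patients with organic neurological disorders recruited by Unit 1 and 2", and names no method for this.

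**What aim 2 promises.** Section 3 gives two objectives. One is the algorithm's specificity for FMD. The other is: "The results obtained will determine which biomarkers are specific for FMD diagnosis identifying the key differences between FMD and patients with" organic motor disorders. Section 7 makes the differences among FMD, HC and organic disorders an endpoint.

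**What is measured, and when.** Under section 10 the algorithm is built in months 10–12 and organic patients are assessed in months 13–22. The Abstract, section 4 (experimental design 2) and section 10 all limit their assessment to the biomarkers in the algorithm.

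**Matching.** For aim 1: "Healthy controls, matched for age and sex, will be recruited through public advertisements". No matching is stated for the organic group.

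**The concern.** The training contrast decides what a classifier and its feature importances mean. Trained on FMD versus HC, the algorithm favours whatever differs between those groups. That may be a feature of FMD, or a feature of having any motor disorder, and the training data cannot tell the two apart. Applying the locked rule to organic patients shows how often it wrongly labels them FMD. It does not re-rank the biomarkers for the new contrast.

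Two errors can follow if the plan is read literally. A marker shifted equally in FMD and organic disease can be reported as specific to FMD. A marker that separates FMD from organic disease but is unremarkable against HC drops out in months 10–12 and is never recorded in organic patients. The choice between FMD and another motor disorder is the one that would make the tool diagnostic, so a wrong list of FMD-specific markers would weaken the main claim of the project.

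**Working it through.** **Inputs from the protocol.** Development set 75 FMD + 75 HC; validation set 75 FMD + 75 HC; organic group 150 (50 per disease), from sections 2, 4, 11 and 12. The Abstract gives 75 organic patients; I use the 150 of the body text. Section 11 sets the organic number only as similar in size to the other groups, with no alpha, power or target specificity, so there is no planned figure to reproduce.

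**Assumptions.** The protocol gives no biomarker distributions. Below, markers are independent, normal, with unit SD and HC mean 0. The shifts are chosen for illustration.

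**1. One marker.** AUC = Φ(difference in means/√2). With an FMD shift of 0.8 and the cut-off halfway, at 0.4, sensitivity and specificity against HC are both Φ(0.4) = 0.66. AUC against HC is Φ(0.8/√2) = 0.71.

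| Organic shift | AUC, FMD vs organic | Specificity in organic |
|---|---|---|
| 0 | Φ(0.8/√2) = 0.71 | Φ(0.4) = 0.66 |
| 0.4 | Φ(0.4/√2) = 0.61 | Φ(0) = 0.50 |
| 0.8 | Φ(0) = 0.50 | Φ(−0.4) = 0.34 |

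The marker's standing against HC is the same in every row. Its value against organic disease runs from unchanged to nil. When the shift is fully shared, specificity in organic patients equals 1 minus sensitivity.

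**2. Several markers.** Simulation of a linear discriminant rule, 75 per group for training, 2000 repetitions. Marker A is shifted in both FMD and organic disease, B only in FMD, C only in organic disease. Weights are mean absolute values; about 0.17 is noise.

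| Shifts A, B, C | Locked rule: sensitivity / specificity HC / specificity organic | Locked weights A, B, C | Direct FMD-vs-organic model: sensitivity / specificity | Direct weights A, B, C |
|---|---|---|---|---|
| 1.5, 0, 1.5 | 77% / 77% / 23% | 1.54, 0.17, 0.17 | 77% / 77% | 0.18, 0.17, 1.55 |
| 1.5, 0.5, 1.5 | 78% / 78% / 27% | 1.54, 0.51, 0.18 | 78% / 78% | 0.17, 0.52, 1.55 |
| 1, 1, 1 | 75% / 76% / 50% | 1.02, 1.04, 0.17 | 75% / 76% | 0.17, 1.03, 1.03 |
| 0, 1.5, 1.5 | 77% / 77% / 76% | 0.17, 1.55, 0.17 | 85% / 85% | 0.20, 1.53, 1.54 |

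In the third row the locked rule weights A and B alike, although only B separates FMD from organic disease. In the last row specificity in organic patients looks good, yet C is missed.

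**3. What a refit can recover.** Take the third row without estimation error.
- Locked score A + B: group means 2 and 1, variance 2 each, so AUC = Φ(1/√4) = 0.69.
- Refit on the markers selected against HC (A and B), which reduces to B: AUC = Φ(1/√2) = 0.76.
- Refit on all three, score B − C: means 1 and −1, variance 2 each, so AUC = Φ(2/√4) = 0.84.

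The first gain needs analysis only. The second needs C to be measured in organic patients.

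**4. Precision.** With 75 FMD and 150 organic patients, the Hanley–McNeil 95% half-width is 0.071 at AUC 0.75 and 0.066 at AUC 0.80. For specificity in all 150, exact 95% intervals are 62–77% at an observed 70% and 84–94% at 90%. In one group of 50 they are 55–82% and 78–97%. For 40/50 = 80% the Wilson interval is 67–89%.

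**The case against.** The strongest reply is that testing a locked algorithm in 150 organic patients is the standard way to estimate specificity, and that specificity is a stated objective of aim 2. That stands. The reply also notes that section 12 speaks of testing the biomarkers, not only the class label, that their values will exist in both FMD and organic patients, and that testing uses explainability methods. A marker-by-marker comparison is therefore open, and its details may sit in a statistical analysis plan that is not at hand.

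This rules out several stronger readings that a reader might infer:
- That aim 2 can show nothing about FMD versus organic disease, or yields only a false-positive rate. The wording of section 12 leaves room for a direct comparison.
- That a poor result could not be interpreted. Low specificity would mean that the algorithm picks up features shared with other motor disorders.
- That the organic group is unmatched and the comparison confounded by age. The protocol states no matching, which is not the same as saying there is none, and it gives no ages. Age is a reason to adjust, not a demonstrated bias.
- That the named features are in fact abnormal in tremor, dystonia or muscle disease. The protocol gives no data on this.

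The appeal to a later analysis plan does not settle the matter. The protocol itself fixes the training contrast, the reuse of the same algorithm, the restricted measurement and the conclusion to be drawn. No analysis plan can recover markers that were not measured in organic patients.

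**Conclusion.** The point holds in a limited form. The procedure described serves the specificity objective. It does not by itself serve the objective of identifying which biomarkers separate FMD from organic disease, because output and feature importances from an FMD-versus-HC model do not answer that question. The search is also confined to markers already selected against HC.

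The size depends on how far marker shifts are shared, which the protocol does not give. In the one-marker example, AUC against organic disease runs from 0.71 with no sharing to 0.50 with full sharing, with no change in the marker's standing against HC. The simulation uses a linear rule, whereas the protocol plans tree-based and instance-based learners, so its weights are illustrative. The central argument does not depend on the learner: a marker with the same distribution in FMD and organic disease can rank high against HC and, taken alone, does not separate FMD from organic disease. The plan should be changed, but aim 2 is not without value as it stands.

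**What to change.** In section 12, state for aim 2:

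1. **Specificity.** Report specificity at the locked cut-off and the AUC of the locked score in the 75 validation-set FMD versus the 150 organic patients, overall and per disease group. The validation set is the right FMD group because the development patients shaped the score.
2. **FMD-specific markers.** Base any such claim on direct per-biomarker FMD-versus-organic contrasts adjusted for age, sex and unit, and on an FMD-versus-organic or three-class model refitted with nested cross-validation on the biomarkers measured in both groups.
3. **Otherwise, a narrower conclusion.** Limit the aim 2 conclusion to specificity, bring section 3 (Specific aim 2) and section 7 into line, and state that hallmarks are sought only among biomarkers preselected for FMD versus HC.

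**Cost.** Items 1 and 2 are additional analysis on biomarkers that the protocol already plans to measure. Per-disease estimates will be imprecise (67–89% around 80% specificity in 50 patients), and item 3 narrows the claim. Extending the refit to the full feature set is not part of this inexpensive change: it would need extra testing of the organic patients, decided before their assessments start in month 13.

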#### **Experimental design aim 3**

A prospective longitudinal study on 34 out of 75 patients with a definite diagnosis of FMD (aim 1) randomly recruited by Unit 1 will be performed. The diagnostic biomarker algorithm resulting from experiment 1 will be tested in patients with FMD before (T0) and after 3 months (T1) of a rehabilitation protocol validated at Unit 1 (WP5) (13). A physician expert in movement disorders will assess patients at each time point through validated clinical scales to assess motor and non-motor symptoms, depression, anxiety, alexithymia, and QoL

as reported in the Methodologies section. A task-based fMRI paradigm to evaluate functional brain reorganization of sensorimotor and non-motor networks induced by rehabilitation and correlations with clinical improvement will be implemented and performed before rehabilitation (T0) and at 3-month follow-up (T1) (5,6). fMRI data will be analyzed by Unit 3. The diagnostic biomarker algorithm through XAI methods will be tested by Unit 2 before and after rehabilitation.

